#### Database and data monitoring

The database will be created using EnnovClinical® software and the access will be secured (personal ID and password required) with different levels of security depending on the role of the investigator. Access will be permitted for the hematologist and the APA instructor (with limited access on their outcomes), the trained interviewers (with limited access on outcome measurement due to blinding), clinical research associate (read-only), methodologist (read-only), and biostatistician (read-only). The clinical research associate of the Methodology and Data Management Centre will visit the hematology unit twice during the protocol and once at the end to verify all consent forms, compliance with established protocol and procedures, and data quality in the eCRF. A data validation plan, jointly defined between the coordinating investigator and the Methodology and Data Management Centre, will be developed and will describe in detail the controls to be performed for each variable. Once the data has been entered, data consistency will be evaluated, and any omissions or inconsistencies will be declared.

Adverse effects and serious adverse effects will be identified according to standard guidelines, recorded in the eCRF and transmitted to the research partners by the main investigator. Patient safety is paramount and any complications and adverse events will be reported and analyzed.

#### Statistical analysis

To evaluate effectiveness of HRVB, we will compare the average evolutions (T3-T1 difference score) between the experimental group (HRVB+APA) and the control group (APA). Student’s t-test will be performed for the different dimensions and scale sub-scores of each questionnaire, as well as cardiac coherence score and SDNN. An analysis of longitudinal data collected at T1, T2, T3 and T4 will be conducted using a linear mixed model with structured covariance residuals. The bivariate survival analysis (death and / or relapse, survival without serious infectious events) will be carried out using the Kaplan-Meier method. Group comparison will be calculated using the log-rank test.

All hypotheses will be tested in a single analysis, intention to treat (according to the group assigned by the randomization), bilaterally at the threshold α = 5%. The analyses will be performed with SAS® (version 9.4, SAS Institute Inc., Cary, NC, USA). At the end of the research study, investigators will anonymize the collected data and results will be submitted to the research partners. The statistician, methodologist and investigators will have access to the final dataset. An article in a journal indexed on Medline will be carried out in post-trial.

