### Data collection and statistical analysis

#### Sample size

Based on a large study among 2800 hematologic patients [6], we expect an additional increase of 5 points, with a standard deviation of 7 points, in the QLQ-C30 score of the experimental group (HRVB+APA) after the 12-week intervention. Due to an estimated 10% missing data rate and dropout rate (abandonment, death, loss of sight), we aim to include 70 patients in the protocol (Fig. 3). They will be randomly assigned to one of two treatment groups (HRVB+APA (*n* = 35) versus APA only (n = 35)). Sample size was calculated with PASS 11® software (power analysis and sample size) to show a significant difference in improvement of quality of life in the experimental group with an alpha level of 5% and a statistical power of 80%.

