#### Blinding and intervention assignment

The specificity of the HRVB and APA interventions will not allow for the use of double-blind assignments for the APA instructor and hematologists. However, we will establish a blinding on the questionnaire assessments for the trained interviewers to maintain a high level of evidence.

Randomization will be balanced in both groups, with a 1:1 allocation ratio, without stratification. The randomization list will be established by the statistician from the Methodology and Data Management Centre before the start of the research. Different sizes of randomization blocks will be used to leave the investigators blind to their size and to avoid predictable allocation. Randomized block sizes of 4,6,8 or 10 blocks will be performed on STATA®. The randomization list will then be imported into the CsRandom module of the Ennov Clinical® electronic case report form (eCRF), which the investigator will use to perform the randomization.

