## Discussion

Previous studies have investigated the effectiveness of HRVB compared to physical exercise [67–69]. To the best of our knowledge, there have been no studies about the added value of HRVB on physical exercise to enhance overall quality of life. While recent studies about HRVB training have demonstrated the feasibility and the effectiveness of HRVB in chronic patients [37, 41, 42], it has not yet been done in cancer patients, namely in hematology. Most clinical studies conclude that HRVB can reduce symptomatology of chronic disease and improve HRV level, supporting our hypothesis that HRVB may be feasible and effective in recovery of hematologic patients.

We hypothesize that HRVB associated with an APA program will be more effective than an APA-only program in improving quality of life during post-treatment in adult hematologic patients and expect the following outcomes from this experimental group: i) significant improvements in overall quality of life and a reported decrease in overall fatigue, anxiety and depression; ii) increased HRV levels, reflecting a better physiological regulation through autonomic control of the heart; iii) better BMI and BP measurements; and iv) less infectious events, relapses and deaths. All of these variables should be improved between T1 and T3. The results recorded at T3 could be sustained through T4, especially if patients are persistent with their home-based practice for both cardiac coherence and physical exercise.

All participating patients will be in remission for hematologic malignancies that have required hospitalization, caused sudden disruptions to their day-to-day lives, and/or have required particular aggressive treatments with high-dose chemotherapy, affecting patients’ overall quality of life. To avoid age-related effects, we have chosen a within-subject design and will exclude patients over 70 years.

Our short-term HRV recording protocol is based on the recommendations from Task Force [70] and more recently from Laborde [57], who has suggested guidelines for psychophysiological research. Although electrocardiogram is more accurate, we use the pulse sensor to assess pulse-to-pulse interval data which accurately approximates the inter-beat interval [71]. To analyze HRV data in time-domain and frequency domain, *HRVanalysis* will be used [58].

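### The effectiveness test is an unadjusted t-test on T3-T1 change; it is valid, but adjusting for the T1 score already collected would generally be more precise

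*Protocol article*

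**What the plan says.** The Statistical analysis section of the protocol article sets the effectiveness contrast: "we will compare the average evolutions (T3-T1 difference score) between the experimental group (HRVB+APA) and the control group (APA" arms. The test follows in the next sentence: a Student's "t-test will be performed for the different dimensions and scale sub-scores of each questionnaire", and also for the cardiac coherence score and SDNN. No covariate is named. Tests are two-sided at 5%, by intention to treat.

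The same section adds a second analysis: "An analysis of longitudinal data collected at T1, T2, T3 and T4 will be conducted using a linear mixed model with structured covariance residuals". It is not designated as the effectiveness test. The text mentions neither the T1 score as a covariate nor a constraint that both arms share one T1 mean.

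Three other places bear on the point:

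- Evaluation times and implementation: the questionnaires, HRV level and cardiac coherence score are all measured at T1 as well as at T3.
- Blinding and intervention assignment: "Randomization will be balanced in both groups, with a 1:1 allocation ratio, without stratification".
- Sample size: "we expect an additional increase of 5 points, with a standard deviation of 7 points, in the QLQ-C30 score", with 10% missing data and dropout, 80% power and 70 patients. It does not say whether 7 is the SD of the change or of the score.

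**The concern.** A t-test on T3-T1 subtracts the whole T1 score, so it fixes the baseline slope at 1. ANCOVA estimates that slope from the data. If the true slope is below 1, as it is when T1 and T3 have similar spread and are imperfectly correlated, full subtraction adds T1 noise to the contrast. That has two consequences.

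- **Precision.** The standard error is larger than it needs to be. The sample size only just reaches 80% power, so the loss is worth avoiding.
- **Chance imbalance.** If the arms differ at T1 by luck, the change-score contrast moves with that difference. About 31 patients per arm are expected to be evaluable, and allocation is not stratified, so nothing in the design limits such a difference in baseline quality of life.

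**Working it through.** **Inputs from the article:** difference 5, SD 7, two-sided alpha 5%, power 80%, dropout and missing data 10%, total 70. Evaluable patients: 70 × 0.9 = 63, or 31.5 per arm. **Assumed, because the article does not give it:** rho, the T1-T3 correlation, taken as 0.3 to 0.9.

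**1. The plan's own figure.** Normal approximation: n per arm = 2(1.960 + 0.842)² × 7²/5² = 30.8, rounded up to 31. Inflated for dropout: 31/0.9 = 34.4, rounded up to 35 per arm, 70 in total. The stated figure is reproduced. (The exact t calculation gives 32 per arm, 36 after inflation, 72 in total.)

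**2. Power of the planned test.** Take 7 as the SD of the change. The standard error is 7 × √(2/31.5) = 1.76, the noncentrality is 5/1.76 = 2.83, and there are 61 degrees of freedom. Power is 79.7%.

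**3. Variance ratio.** With common variance s² at T1 and T3:

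- change score: 2s²(1 − rho)
- ANCOVA residual: s²(1 − rho²) = s²(1 − rho)(1 + rho)
- ratio, ANCOVA to change: (1 + rho)/2, which is below 1 for every rho below 1.

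**4. Power with ANCOVA.** Residual SD = 7 × √((1 + rho)/2), with 60 degrees of freedom:

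| rho | variance ratio | residual SD | power | total for 80% power, after 10% inflation | implied score SD |
|---|---|---|---|---|---|
| planned t-test | 1 | 7.00 | 79.7% | 72 | – |
| 0.3 | 0.65 | 5.64 | 93.3% | 49 | 5.9 |
| 0.5 | 0.75 | 6.06 | 89.6% | 56 | 7.0 |
| 0.7 | 0.85 | 6.45 | 85.7% | 63 | 9.0 |
| 0.9 | 0.95 | 6.82 | 81.6% | 69 | 15.7 |

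The last column is 7/√(2(1 − rho)), the between-patient SD that a change SD of 7 implies. A simulation with 31 per arm gave variance ratios of 0.66, 0.76 and 0.89 at rho 0.3, 0.5 and 0.7. These are close to the formula and slightly above it, so the ANCOVA powers are, if anything, a little generous.

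**5. If 7 is instead the SD of the score.** Change-score power against ANCOVA power is 65.5% and 83.2% at rho 0.3, 79.7% and 89.6% at 0.5, and 95.0% and 97.4% at 0.7. ANCOVA is ahead under either reading.

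**6. Chance imbalance, illustrated at rho 0.5.** The score SD is then 7, so one standard error of the T1 difference is 7 × √(2/31.5) = 1.76 points. An imbalance of that size shifts the change-score contrast by (1 − 0.5) × 1.76 = 0.88 points, against a target of 5. ANCOVA removes this shift.

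**7. The mixed model.** If T1 enters as an outcome and each arm has its own T1 mean, then in complete data the model's T3-T1 group contrast equals the difference in mean change. It gains the precision only with a common T1 mean or with T1 as a covariate.

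**The case against.** The strongest reply is that nothing here is invalid. The change-score t-test is unbiased under randomization, it matches the way the sample size was planned, and the trial reaches its stated power with it if 7 is the SD of the change. All of that stands; the point concerns efficiency only.

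The size of the gain is also uncertain. The low-rho rows imply a score SD of only 5.9 to 9.0 on a 0-100 scale. A mixed hematologic population could well be more variable. A score SD of about 15.7, also an assumption, would put rho at 0.9 and the gain at about 2 points. This stands too, and is why the whole range is shown.

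The mixed model may be set up with baseline adjustment in an analysis plan that is not shown. That softens the point but does not remove it, because the article itself assigns the effectiveness question to the t-test.

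A reader might infer more than the article supports:

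- *That the test is biased.* The shift in step 6 is conditional on a T1 imbalance that has occurred. Averaged over randomizations it is zero.
- *That change scores over-correct whenever rho is below 1.* The baseline slope is rho × SD(T3)/SD(T1). At rho 0.7 and an SD ratio of 1.43 it equals 1, and the change score is then optimal. The (1 + rho)/2 ratio needs roughly equal variances.
- *That the test adjusts for nothing, so age must be added.* The Discussion says "To avoid age-related effects, we have chosen a within-subject design and will exclude patients over 70 years", which is loose wording for a parallel-group trial. Differencing nevertheless removes stable differences in level between patients, and nothing in the article shows that age predicts change in quality of life.

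**Conclusion.** The point holds as a loss of precision, not of validity. An unadjusted change-score t-test is fixed as the effectiveness test although a generally more efficient analysis is available from data already being collected. Under equal T1 and T3 variances, a change SD of 7 and 63 evaluable patients, the gain in power is about 2 to 14 percentage points: from about 80% to 82% at rho 0.9 and to 93% at rho 0.3. Since rho is not documented, no single figure in that range can be claimed. Protection against chance T1 imbalance is a further benefit. The change is worth making because it costs so little, but the trial is not unsound without it.

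**What to change.** Before any unblinded analysis, replace the t-test on T3-T1 by an ANCOVA of the T3 score on randomized group and T1 score, for the questionnaire scores, SDNN and the cardiac coherence score. Equivalently, take the T3 group contrast from the planned mixed model, stating that it has either T1 as a covariate or a common T1 mean for both arms, and name that contrast as the effectiveness analysis. State also whether the planning SD of 7 is that of the change or of the score.

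The cost is one degree of freedom, with no further data or patients. It does need a short protocol amendment, since the Design and setting section requires modifications to be written as an amendment and validated by the ethics committee.

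### The effectiveness test compares raw T3-T1 change without adjusting for the T1 score, which gives up precision and lets chance baseline imbalance move the estimate

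*Protocol article*

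**What the plan says.** The Statistical analysis section fixes the effectiveness comparison: "we will compare the average evolutions (T3-T1 difference score) between the experimental group (HRVB+APA) and the control group (APA"). The test is Student's t-test, which "will be performed for the different dimensions and scale sub-scores of each questionnaire, as well as cardiac coherence score and SDNN". No adjustment for the T1 value is mentioned.

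A second analysis is listed after it: "An analysis of longitudinal data collected at T1, T2, T3 and T4 will be conducted using a linear mixed model with structured covariance residuals". It is not named as the effectiveness test, and neither a T1 covariate nor a common T1 mean across arms is stated for it.

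The Sample size section gives the planning values: "we expect an additional increase of 5 points, with a standard deviation of 7 points, in the QLQ-C30 score of the experimental group", "with an alpha level of 5% and a statistical power of 80" per cent. Testing is "bilaterally at the threshold α = 5" per cent. The Blinding and intervention assignment section describes randomisation "with a 1:1 allocation ratio, without stratification". Under Evaluation times and implementation, quality of life is scheduled at T1, T2, T3 and T4.

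**The concern.** A t-test on T3 minus T1 assumes that each extra point at T1 carries over as exactly one point at T3. With similar spread at both visits, the real slope equals the T1-T3 correlation, which is below 1 for imperfectly reliable scores 12 weeks apart. Patients who start low then tend to gain more through regression to the mean alone, and subtracting T1 over-corrects.

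Two things follow. First, the change-score estimate has a larger variance than an estimate adjusted for T1, so the trial has less power and wider intervals than its data allow. Second, if the arms differ at T1 by chance, the arm that starts lower looks better than it should. Allocation is not stratified, so nothing in the design balances T1 quality of life. Neither effect depends on dropout or on the choice of analysis set.

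**Working it through.** **Inputs.** Effect 5 points, SD 7 points, 80% power, 10% loss and 70 patients (Sample size section); two-sided alpha of 5% (Statistical analysis section). The T1-T3 correlation, rho, is not in the document and is taken as 0.3 to 0.8. Equal SDs at T1 and T3 are assumed.

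**1. The planned size reproduces.** By the normal approximation, n per arm = 2 × (1.96 + 0.84)² × 7² / 5² = 30.8, so 31. Allowing for 10% loss, 31 / 0.9 = 34.4, so 35 per arm and 70 in all. The noncentral t needs 32 per arm, or 72 in all. The sample size is not in dispute.

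**2. Precision with 7 as the SD of change.** If sigma is the SD of a single score:
- SD of change = sigma × √(2(1 − rho)) = 7
- residual SD after T1 adjustment = sigma × √(1 − rho²) = 7 × √((1 + rho)/2)
- variance ratio, adjusted to change score = (1 + rho)/2

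Power is from the noncentral t with 31 per arm, taking off one degree of freedom for the covariate. The planned t-test has 79.0%.

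| rho | Residual SD | Variance ratio | Power, adjusted | CI narrower by | Total N for 80% power after 10% loss |
|---|---|---|---|---|---|
| 0.3 | 5.64 | 0.65 | 92.9% | 19% | 50 |
| 0.5 | 6.06 | 0.75 | 89.1% | 13% | 56 |
| 0.7 | 6.45 | 0.85 | 85.1% | 8% | 64 |
| 0.8 | 6.64 | 0.90 | 83.0% | 5% | 66 |

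At rho 0.5 the 62 evaluable patients do the work of 62 / 0.75, or about 83, analysed by change score. Using 63 evaluable patients (70 × 0.9) moves each power by less than one point: 79.7% planned, against 93.3%, 89.6%, 85.7% and 83.6%. Estimating the slope also inflates the adjusted variance on average by 1 + 1/58 (62 patients less 4 gives 58), which lowers the adjusted powers in the table by less than one point.

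**3. Precision with 7 as the SD of a single score.** The protocol does not say which SD is meant. On this reading the SD of change is 7 × √(2(1 − rho)) and the residual SD is 7 × √(1 − rho²). Power for change score against adjusted is 64.8% against 82.6% (rho 0.3), 79.0% against 89.1% (0.5) and 94.6% against 97.2% (0.7).

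**4. Effect of a chance T1 imbalance.** Given a T1 difference D between arms, the change-score estimate shifts by −(1 − rho) × D. With 7 as the SD of change, sigma = 7 / √(2(1 − rho)), and the standard error of D is sigma × √(2/31).

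| rho | sigma | 1 SE of D | Shift at 1 SE | Shift at 1.96 SE |
|---|---|---|---|---|
| 0.3 | 5.92 | 1.50 | 1.05 | 2.06 |
| 0.5 | 7.00 | 1.78 | 0.89 | 1.74 |
| 0.7 | 9.04 | 2.30 | 0.69 | 1.35 |

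At rho 0.5 the 1.96-SE shift is 1.74 / 5 = 35% of the target effect, which is also the protocol's minimal clinically important difference for the QLQ-C30.

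**5. Whether the mixed model recovers this.** Not as described. With T1 as an ordinary outcome, arm means left free at T1 and complete data, its T3-minus-T1 contrast between arms equals the difference in mean change. It gains the precision only with T1 as a covariate or a common T1 mean.

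**The case against.** The planned test is not an error. Under randomisation it holds its type I error and is unbiased on average. It matches the quantity the trial was sized for, and it reaches about its planned power. All of this stands: what is lost is precision.

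The shift in step 4 is conditional on the imbalance drawn. It can go either way and averages to zero, and a 2-SE imbalance arises in only about 5% of trials. That stands too, although an imbalance of at least 1 SE arises in about 32%.

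The size of the gain is uncertain. Rho and the visit-specific SDs are not given, a slope below 1 is plausible but not guaranteed if scores spread out by T3, and the meaning of the 7 points is open. At rho 0.8, or on the single-score reading at rho 0.7, power rises by only about 3 to 4 points. Adjustment gains in every scenario computed, but the amount cannot be pinned down.

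T1 is a clean covariate only if it is measured before allocation is known, and the protocol places consent, randomisation and the questionnaires all at T1. This is worth confirming, but a T1 score taken after allocation would compromise the change score as well.

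Finally, the detailed form of the mixed model could be left to an analysis plan. The t-test on change could not: the protocol names it.

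**Conclusion.** The concern holds, as a loss of efficiency in a valid analysis. For rho between 0.3 and 0.8 and equal variances at T1 and T3, adjusting for T1 cuts the variance by 35% to 10%. With 7 as the SD of change, it raises power from about 79% to between 93% and 83% at the same number of patients. The single-score reading points the same way. A one-standard-error T1 imbalance moves the planned estimate by about 0.7 to 1.1 points, against a target of 5. In a single-centre trial of 70 patients, powered at about 80% with an active comparator, the change should be made, and before any outcome data are seen.

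**What to change.** In the Statistical analysis section, replace the t-test on T3-T1 difference scores with a linear model of the T3 score on arm and T1 score (ANCOVA), reporting the adjusted difference with its 95% CI. Use the same form for the secondary questionnaire scores, SDNN and cardiac coherence score. In the T1-T4 mixed model, either enter T1 as a covariate or constrain the arms to a common T1 mean, so that both analyses estimate the same adjusted effect at T3. State that the T1 questionnaires are completed before allocation is disclosed, and whether the SD of 7 points refers to change or to a single score.

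The cost is about one sentence for the analysis and one for each clarification, with no new data and no more patients. The headline becomes an adjusted difference, still in QLQ-C30 points. Keep n = 70. If 7 is the SD of change, the stated 80% power becomes conservative over the range shown.

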**Methods:**

Seventy patients aged 18–70 years, with various forms of hematological malignancies, in post-treatment remission within six months prior to beginning the study and who have been prescribed APA by a hematologist, will be randomly allocated in a 1:1 ratio to two 12-week treatment groups: HRVB + APA versus APA alone. APA sessions will consist of aerobic and resistance training for 1-h twice weekly. The HRVB training will consist of controlled breathing exercises with biofeedback of heart rate variability for 10 sessions and will include a daily home-based practice. The primary outcome will be to evaluate health-related quality of life (QLQ-C30, SF-36). The secondary outcomes will be to evaluate fatigue (MFI-20); anxiety and depression (HADS); clinical status with blood pressure, progression-free survival, overall survival, and body mass index; heart rate variability level and cardiac coherence score. All of these assessments will be evaluated initially (T1), 6 weeks after (T2), at the end of the 12 weeks (T3), and then at a 12-week post-intervention follow-up (T4).

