### Objectives and outcomes

Our protocol evaluates the superiority of an adapted physical activity (APA) program combined with HRVB (experimental group), over a program with APA only (control group). The APA program is suggested for hematologic patients as a supportive cancer care by the ACSM exercise guidelines for cancer survivors [14] and has also been recommended specifically for patients undergoing HSCT [16].

The primary objective will be to investigate the effects of a 12-week intervention of HRVB associated with an APA program versus APA only on overall quality of life measured with Quality of Life Core Questionnaire (QLQ-C30) in hematologic patients. Specifically, we will evaluate the effects on fatigue, anxiety and depression; assess clinical status with BP, progression-free survival, overall survival, and body mass index (BMI); and measure HRV level, cardiac coherence score, physical condition, satisfaction, and adherence to the protocol (to ensure the quality of support provided to patients).

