### Assessments

#### Quality of life assessment

Quality of life will be evaluated with the QLQ-C30 version 3.0 developed by the European Organization for Research and Treatment of Cancer [8]. The QLQ-C30 incorporates 5 functional scales (physical, role, cognitive, emotional, and social); 3 symptom scales (fatigue, nausea/vomiting, and pain); 6 single-items (dyspnea, insomnia, appetite loss, constipation, diarrhea, and financial difficulties); and a global health subscale. Scores will be transformed to a 0–100 scale, with 100 reflecting highest functioning, highest symptomatology or highest global health, according to each scale. The minimal clinically important difference (MCID) is at least 5 points to achieve a clinically significant improvement [48].

To complement this assessment, the Medical Outcomes Study 36-Items Short-Form Health Survey (SF-36) will also be used [43]. The French validated version [49] contains 8 scales: physical functioning, role limitations (physical), bodily pain, general health, vitality, social functioning, role limitations (emotional), and mental health, which may be gathered in 2 second-order factors consisting of a mental component summary and a physical component summary. For each dimension, item scores will be coded, totaled, and transformed to a 0–100 score where the lowest score of 0 will correspond to ‘least healthy’ and the highest score of 100 will correspond to ‘healthiest’, with an estimated MCID of 3 points [50].

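### The primary outcome is stated inconsistently, no single QLQ-C30 score is named as primary, and the analysis section tests every sub-score at 5% without a decisive test

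*Protocol article*

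**What the plan says.** Five places in the protocol article bear on this point.

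- **Abstract, Methods:** "The primary outcome will be to evaluate health-related quality of life (QLQ-C30, SF-36"). Two instruments, no scale named. The same paragraph lists fatigue, anxiety and depression, heart rate variability and coherence score as secondary.
- **Objectives and outcomes:** the primary objective is the effect "on overall quality of life measured with Quality of Life Core Questionnaire (QLQ-C30) in hematologic patients". One instrument, no scale named.
- **Quality of life assessment:** the QLQ-C30 has "5 functional scales (physical, role, cognitive, emotional, and social); 3 symptom scales (fatigue, nausea/vomiting, and pain); 6 single-items" "and a global health subscale". No total score is described. The SF-36 enters in a supporting role: "To complement this assessment, the Medical Outcomes Study 36-Items Short-Form Health Survey (SF-36) will also be used".
- **Sample size:** an additional increase of 5 points with a standard deviation of 7 is expected "in the QLQ-C30 score of the experimental group (HRVB+APA) after the 12-week intervention". Which score is meant is not said.
- **Statistical analysis:** the T3-T1 change is compared between groups by Student's t-test, which "will be performed for the different dimensions and scale sub-scores of each questionnaire, as well as cardiac coherence score and SDNN". A linear mixed model on T1 to T4 follows and is not ranked against the t-test. All hypotheses are tested "bilaterally at the threshold α = 5" percent.

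**The concern.** A confirmatory trial needs one result that decides whether it succeeded. Here the instrument differs between abstract and objectives, the scale within the instrument is left open, and the analysis section treats all scores alike and offers two methods for them. An analyst who followed the text could report a significant result on any QLQ-C30 scale (or, on the abstract's wording, any SF-36 scale) as the primary finding without departing from the plan.

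Two things are at stake. The 5% level does not describe the risk of a false main claim. And the 80% power belongs to a single test that the analysis section never singles out, so nobody can check that the assumed difference and standard deviation fit the score that will be used.

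**Working it through.** **1. Reproduce the sample size.** Inputs from the Sample size section: difference 5, SD 7, alpha 5%, power 80%, 10% missing data and dropout. The Statistical analysis section makes the tests two-sided.

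- Normal approximation: n per arm = 2 × (1.960 + 0.842)² × 7² / 5² = 30.8, so 31. Total 62; 62 / 0.9 = 68.9, so 69.
- Noncentral t: 32 per arm; 64 / 0.9 = 71.1, so 72.
- One-sided variant: 25 per arm, 56 in total, which does not match.

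The planned 70 lies between 69 and 72. It therefore corresponds to **one** comparison at two-sided 5%.

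**2. Count the scores that could carry the primary claim.**

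- QLQ-C30: 5 functional + 3 symptom + 6 single items + 1 global = **15** (reading of the objectives).
- SF-36: 8 scales + 2 component summaries = 10. With the QLQ-C30: 15 + 10 = **25** (reading of the abstract). The summaries are optional in the text; without them the count is 15 + 8 = 23.

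**3. Chance of at least one false positive when HRVB adds nothing.** If independent, this is 1 − 0.95^k in either direction, and 1 − 0.975^k for a result in favour of HRVB. Quality-of-life scales are correlated, but the documents give no correlations, so 0.3 to 0.7 is an assumed range. For that range, k test statistics were simulated (100,000 draws) as Z_j = √r·U + √(1−r)·e_j, with U and e_j standard normal, and |Z_j| > 1.96 counted as significant.

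| Scores | Direction | Independent | r = 0.3 | r = 0.5 | r = 0.7 |
|---|---|---|---|---|---|
| 15 | either | 1 − 0.95^15 = 54% | 46% | 36% | 26% |
| 15 | favours HRVB | 1 − 0.975^15 = 32% | 24% | 18% | 13% |
| 25 | either | 1 − 0.95^25 = 72% | 61% | 47% | 32% |
| 25 | favours HRVB | 1 − 0.975^25 = 47% | 32% | 23% | 16% |

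A single named test would give 5% in either direction and 2.5% in favour of HRVB. Of the two-sided figures, the share favouring HRVB runs from about half (r = 0.7) to 47 / 72 = 65% (25 independent scores). The mixed model gives a second route to significance for the same outcomes and is not counted here.

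**4. Compare the sections on the instrument.** Objectives, assessment section and sample size all point to the QLQ-C30; the abstract's parenthesis is the outlier. No section settles the scale.

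**The case against.** The body of the protocol is consistent on the instrument, and the SF-36 is described there as complementary. The contrast is largely fixed too: T3-T1, after 12 weeks. Overall quality of life can be read as the global health subscale. The document is a condensed article, an analysis plan may exist, and unadjusted tests of secondary scores are not in themselves an error.

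Much of this stands. It narrows the conflict over instruments to the abstract, and it means that missing adjustment of secondary scores is no fault. It does not supply the missing scale: the document never says that the global subscale is primary. Nor does condensation explain two different primary outcomes, or a 5% threshold given for all hypotheses with no test ranked first. Those statements need correcting whatever an analysis plan adds.

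A reader might infer more: that all the tested scores (15 + 10 + 4 fatigue + 2 anxiety and depression + 2 heart rate variability = 33) could each support a claim of success, with a false-positive chance of 1 − 0.95^33 = 82%. The documents do not support that. The abstract labels the last eight as secondary, independence is implausible for overlapping scales, and the figure counts results against HRVB as well.

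A reader might also infer that the trial is underpowered because alpha would have to be split between instruments. No such split is proposed, and the sample size is correct for one test.

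**Conclusion.** The point holds in this form: the primary outcome is stated inconsistently, the decisive QLQ-C30 score is not identified, and the analysis section names neither a decisive test nor which of its two analyses is primary. Among scores eligible for the primary claim, the two-sided false-positive chance is 54% (15 scores) or 72% (25 scores) at most. Under the assumed correlations it is 26% to 46% or 32% to 61%. Even on the narrowest case calculated (15 scores, r = 0.7, favouring HRVB), 13% is about five times the 2.5% of a single test.

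The exact percentages rest on the assumed equal correlations; the inconsistency does not. The planned 70 stands, provided that one score is tested once and the 5-point difference and SD of 7 apply to that score. This should be corrected before the data are analysed.

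**What to change.** - Name one QLQ-C30 score as primary. The global health subscale best fits the wording of the objectives.
- State the contrast (T3-T1 between groups) and one primary analysis, either the t-test or the mixed model, tested once at two-sided 5%. Label the other analysis supportive.
- In the abstract, move the SF-36 to the secondary outcomes. Align the abstract, Objectives and outcomes, Sample size, and Statistical analysis sections.
- Confirm that the 5-point difference and SD of 7 apply to the named score. If they do not, redo the calculation, since the required number varies with (SD / difference)².
- Label all other scores secondary or exploratory, so that they cannot carry the main efficacy claim. Whether to adjust among them is a choice for the analysis plan.

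The cost is wording, made before database lock, with no new data. The trial-off is that fewer scales can support a claim of success.
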